| EVALUATION FOR INTER-CURRENT HIV INFECTION:       | 
Volunteers will be tested for HIV according to the Schedule of Procedures. Test results will be interpreted according to a pre-determined diagnostic algorithm. Should one or more serological HIV test(s) post-vaccination be positive, a nucleic-acid-based HIV test will be performed to distinguish a true HIV infection acquired through exposure in the community from HIV seropositivity due to the vaccine-induced antibody response. HIV testing at additional time points may be performed upon request of the volunteer and principal investigator or designee as medical or social circumstances warrant.
 
To maintain blinding of study staff with direct contact with the volunteers, HIV test results will be reported to the clinical team as “HIV-uninfected” or as “HIV-infected” (ONLY once intercurrent HIV infection is confirmed).
                                                                                                                                                                                                                                                  |
| SAFETY MONITORING AND STATISTICAL CONSIDERATIONS: | 
All clinical trial data collected, identified only by a volunteer identification number, will be entered into a database.
 
Safety will be continually monitored by the Investigators, the Sponsor’s Medical Monitor and a Protocol Safety Review Team (PSRT); detailed stopping criteria are pre-defined.
 
All safety data will be reviewed by an independent Safety Review Board (SRB) once the first 15 volunteers randomized across all groups have reached the M 2.5 and M 6.5 time points.
 
Ad-hoc safety review may be specifically requested by the Sponsor, Profectus, Ichor, the Principal Investigators, Ethics Committees, Regulatory Authorities, or by the SRB.
 
At the end of the study, a full analysis will be prepared according to a pre-specified statistical analysis plan. In addition, there may also be interim reviews of blinded data. All clinical and routine laboratory data will be included in the safety analysis. Immunogenicity analysis will be performed according to a predefined analysis plan for all volunteers who received vaccine or placebo.
 |

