## 4.0 STUDY OBJECTIVES

### 4.1 Primary Objectives

1. To evaluate the safety and tolerability of HIV-MAG with or without co-administered GENEVAX® IL-12 given intramuscularly by *in vivo* electroporation (IM/EP) using the Ichor Medical Systems TriGrid™ Delivery System (TDS-IM), followed by Ad35-GRIN/ENV in each of four different regimens
2. To evaluate the safety and tolerability of Ad35-GRIN/ENV followed by HIV-MAG with co-administered GENEVAX® IL-12 given intramuscularly by *in vivo* electroporation (IM/EP) using the Ichor Medical Systems TriGrid™ Delivery System (TDS-IM)

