## 8.0 INVESTIGATIONAL PRODUCT

### 8.1 Description

- The HIV-MAG vaccine is manufactured by Boehringer Ingelheim (Austria) and supplied by Profectus Biosciences, Inc.
- GENEVAX® IL-12 is manufactured by Cardinal Health (US) and supplied by Profectus Biosciences, Inc.
- The Ad35-GRIN/ENV vaccine is manufactured by Transgene (France) and supplied by IAVI.
- Sodium Chloride Injection, USP 0.9% will be used as placebo for the HIV-MAG and GENEVAX® IL-12 and Ad35 vaccines.
- The TDS-IM electroporation device is manufactured by California MedTech (US) and Life Science Outsourcing (US) and supplied by Ichor Medical Systems, Inc.

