## 10.3 Relationship to Investigational Product

The relationship of an (S)AE to Investigational Product (IP) is assessed and determined by the Principal Investigator or designee. All medically indicated and available diagnostic methods (e.g., laboratory, blood smear, culture, X-ray, etc...) should be used to assess the nature and cause of the AE/SAE. Best clinical and scientific judgment should be used to assess relationship of AE/SAEs to the IP and/or other cause.

The following should be considered:

- Presence/absence of a clear temporal (time) sequence between administration of the Investigational Product and the onset of AE/SAE
- Presence/absence of another cause that could more likely explain the AE/SAE (concurrent disease, concomitant medication, environmental or toxic factors, etc.)
- Whether or not the AE/SAE follows a known response pattern associated with the Investigational Product

The relationship should be reported as one of the following:

**Not Related:** clearly explained by another cause (concurrent disease, concomitant medication, environmental or toxic factors, etc.).

**Unlikely:** more likely explained by another cause (concurrent disease, concomitant medication, environmental or toxic factors, etc.).

**Possibly:** equally likely explained by another cause but the possibility of the Investigational Product relationship cannot be ruled out (e.g., reasonably well temporally related and/or follows a known Investigational Product response pattern but equally well explained by another cause).

**Probably:** more likely explained by the Investigational Product (e.g., reasonably well temporally related and/or follows a known Investigational Product response pattern and less likely explained by another cause).

**Definitely:** clearly related and most likely explained by the Investigational Product.

For the purpose of expedited safety reporting, all possibly, probably or definitely related SAEs are considered Investigational Product-related SAEs.

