#### 10.4 Serious Adverse Events

*An adverse event is reported as a "Serious Adverse Event" if it meets any the following criteria (as per International Conference on Harmonisation [ICH] Good Clinical Practice [GCP] Guidelines):*

- Results in death
- Is life threatening
- Results in persistent or significant disability/incapacity
- Requires in-patient hospitalization or prolongs existing hospitalization
- Is a congenital anomaly/birth defect or spontaneous abortion
- Any other important medical condition that requires medical or surgical intervention to prevent permanent impairment of a body function or structure

Serious Adverse Events (SAEs) should be reported to IAVI within 24 hours of the site becoming aware of the event. All SAEs should be reported using the designated SAE Report Form and sent to the Sponsor as described in the SOM.

To discuss Investigational Product-related SAEs or any urgent medical questions related to the SAE, the site investigator should contact one of the IAVI medical monitors directly (see the Contact List).

The IAVI SAE Report Form should be completed with all the available information at the time of reporting. The minimum data required in reporting an SAE are the volunteer identification number, date of birth, gender, event description (in as much detail as is known at the time), onset date of event (if available), reason event is classified as serious, reporting source (name of Principal Investigator or designee) and relationship to the Investigational Product as assessed by the investigator.

The Principal Investigator or designee is required to write a detailed written report with follow up until resolution or until it is judged by the Principal Investigator or designee to have stabilized. The Principal Investigator or designee must notify the local IRB/IEC of all SAEs as appropriate. In case of Investigational Product-related SAEs, the Sponsor will notify responsible regulatory authorities, Safety Review Board (SRB), and other study sites where the same Investigational Product is being tested.

More details on SAE definitions and reporting requirements are provided in the SOM.

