### **17.1 Protocol Safety Review Team**

The Protocol Safety Review Team (PSRT) will be formed to monitor the clinical safety data. During the vaccination phase of the trial, the PSRT will review clinical safety data on a weekly basis. An *ad hoc* PSRT review meeting will occur if any of the members of the PSRT requests a special review to discuss a specific safety issue or as specified in the Study Operations Manual.

The PSRT will consist of the IAVI Medical Monitor(s) and PI or designee from each clinical team. An IAVI Medical Monitor will be the PSRT Chair. *Ex officio* members will include the IAVI CMO, IAVI Medical Safety Monitor and representatives from Profectus Biosciences Inc. and Ichor Medical Systems, Inc.

Additional PSRT participants may include the following, as needed:

- Co-investigators and CRC senior clinical research nursing staff
- Laboratory directors
- Data management, study statistician and regulatory staff

The Terms of Reference for PSRT and procedures to be followed are detailed in the SOM.

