### **17.3 Criteria for Pausing the Study**

Enrolment and vaccinations will be stopped and a safety review conducted by the SRB for any of the following criteria:

- one subject experiences an SAE that is probably or definitely related to the investigational vaccine(s), or two or more subjects experience similar SAEs which are possibly related to the investigational vaccine(s);
- there is a subject death assessed as possibly, probably or definitely related to the investigational vaccine(s)
- one subject experiences injection site ulceration, sterile abscess or necrosis associated with vaccine administration; or
- one subject experiences a severe allergic reaction, such as laryngospasm, bronchospasm or anaphylaxis, associated with vaccine administration.

The Sponsor will request a review by the SRB, or the SRB chair if other SRB members cannot be convened, to be held within 2 business days of the Sponsor learning of the event. The individual volunteer(s)/or study may be unblinded at the discretion of the SRB.

Following this review, the SRB will make a recommendation regarding the continuation or suspension of the vaccinations or the trial and communicate this decision immediately to the Sponsor. The Sponsor then will inform the Principal Investigators without delay.

Additional *ad hoc* review may be specifically requested by the Sponsor, the Principal Investigator(s) or by the SRB.

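### Pausing criteria 1 and 2 in Section 17.3 turn on relation to the vaccine(s), a narrower term than the causality rating in Section 10.3, so an SAE attributed to the electroporation device alone need not pause the study

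*Protocol*

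**What the plan says.** Section 17.3 lists four events that stop enrolment and vaccination and send the case to the SRB within 2 business days of the sponsor learning of it. The first is met when "one subject experiences an SAE that is probably or definitely related to the investigational vaccine(s", or when two or more volunteers have similar SAEs possibly related to the same vaccine(s). The second is met when "there is a subject death assessed as possibly, probably or definitely related to the investigational vaccine(s". The third and fourth cover injection-site ulceration, sterile abscess or necrosis, and severe allergic reaction. Those two use a wider link, to the administration of vaccine.

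Electroporation is part of what the trial tests. The first primary objective concerns HIV-MAG given "using the Ichor Medical Systems TriGrid™ Delivery System (TDS-IM), followed by Ad35-GRIN/ENV in each of four different regimens", and the second also names the TDS-IM. Section 8.1.5 calls it a Class II device for investigational use.

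Causality is rated once, in Section 10.3, against Investigational Product. The middle grade, possibly, applies when the event is "equally likely explained by another cause but the possibility of the Investigational Product relationship cannot be ruled out".

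The protocol is not consistent on whether the device is Investigational Product:
- Section 8.1, under the heading Investigational Product, includes it: "The TDS-IM electroporation device is manufactured by California MedTech (US". Sections 8.1.5 and 8.2 also cover it there.
- The synopsis list of study vaccines and investigational products omits it.
- Section 7.8 glosses Investigational Product as vaccine or placebo.
- Section 10.5 names study procedures separately from Investigational Product.

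**The concern.** The pausing rule acts on a judgement that the protocol does not collect. Investigators record relation to Investigational Product, while criteria 1 and 2 ask about the vaccine(s). The second term is the narrower one, since the synopsis list counts saline placebo as an investigational product and Section 8.0 describes the device under that heading as well.

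The difference matters for a systemic event blamed on the electrical pulse or the procedure. A vaccine-related SAE of the same certainty stops dosing automatically. For the device event, someone has to choose to act. Stated human experience with this device is just over 90 subjects in electroporation arms (Section 3.4). The exclusion criteria already anticipate such events by ruling out implanted or stimulation devices, arrhythmia, recent syncope and any seizure history. A pre-set pause that reaches the device is reasonable in a Phase 1 safety trial.

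**Working it through.** No plan figure is at issue, so the check sets the texts side by side.

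**Step 1. What each pausing criterion requires (Section 17.3)**

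| Criterion | Event | Link required |
|---|---|---|
| 1, first limb | one SAE | probably or definitely related to the vaccine(s) |
| 1, second limb | two or more similar SAEs | possibly related to the vaccine(s) |
| 2 | death | possibly, probably or definitely related to the vaccine(s) |
| 3 | local ulceration, abscess, necrosis | associated with vaccine administration |
| 4 | severe allergic reaction | associated with vaccine administration |

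The wider link appears only in criteria 3 and 4. No criterion names the device, electroporation or study procedures.

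**Step 2. Apply the criteria to a non-local, non-allergic event after an electroporation visit**

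| Attribution | One non-fatal SAE | Two similar SAEs | Death |
|---|---|---|---|
| Device or procedure, not vaccine (literal reading) | no pause | no pause | no pause |
| Possibly, because pulse and vaccine cannot be separated | no pause | pause | pause |
| Probably or definitely, with the Investigational Product rating used for Section 17.3 and the device counted as product | pause | pause | pause |

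The result for one event therefore depends on an unsettled definition. Two sites could handle the same SAE differently.

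**Step 3. A case where the vaccine can be excluded**

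Placebo for the DNA vaccine is saline given by electroporation (Table 8.1.4-1, Section 8.4). From Table 5.2-1 and Appendices A and B:
- Planned electroporation visits: 45 × 3 + 30 × 1 = 165.
- Of these, in placebo recipients: 9 × 3 + 6 × 1 = 33, and 33/165 = 20%.

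If such a volunteer has an SAE and the assessor learns the assignment, relation to vaccine is ruled out and criteria 1 and 2 cannot be met. This should be rare, because Section 7.9 confines emergency unblinding to those managing the volunteer and keeps study assessors blinded. The 20% is a share of exposures, not an event rate.

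**Step 4. What remains when no criterion is met**

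- All SAEs reach the sponsor within 24 hours (Section 10.4). Also from 10.4: "In case of Investigational Product-related SAEs, the Sponsor will notify responsible regulatory authorities, Safety Review Board (SRB), and other study sites". For a device event this notice depends on the same definition of Investigational Product.
- From Section 17.1: "During the vaccination phase of the trial, the PSRT will review clinical safety data on a weekly basis". Any member of this team (the PSRT) may ask for an ad hoc meeting, and the device supplier is represented ex officio.
- Under the synopsis, an ad hoc "safety review may be specifically requested by the Sponsor, Profectus, Ichor", as well as by investigators, ethics committees, regulators or the SRB. Section 17.3 has a shorter list.
- The sponsor may suspend the study (Section 12.3).
- The scheduled SRB review receives all SAEs (Section 17.2.1), but only once the first 15 volunteers reach set time points.
- Section 12.1 ends dosing for an individual after, for example, convulsions following vaccination. It does not stop the study.

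Some of these steps are obligatory, but none compels a study-level stop or carries the 2-business-day deadline.

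**The case against.** The best reply is that the literal reading does not match how the rule would be used. There is one causality scale, to Investigational Product, and no separate vaccine rating to feed Section 17.3, so in practice the product rating would be applied. Section 8.0 describes the device under that heading, and Section 8.4 treats electroporation as part of administering the product. Section 10.3 does not list delivery among its examples of other causes, so an SAE plainly due to electroporation could be rated probably or definitely related and pause the study. Staff are blinded and the device injects and pulses in one automated sequence, so an investigator could seldom exclude the vaccine.

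Much of this stands, and it is why the gap is narrow. It does not close it. The reply needs two readings that the protocol never states: that vaccine(s) in Section 17.3 means Investigational Product, and that Investigational Product includes the device. The synopsis list and Section 7.8 point the other way on the second. The list of other causes in Section 10.3 is also open-ended.

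A reader might infer more than the text supports:
- That device-related SAEs go unwatched. They do not: the routes in Step 4 are real.
- That a device-related death would generally fail to pause the study. A rating of possibly is enough for a death, and a blinded investigator would often give at least that.
- That electroporation visits between weekly PSRT meetings measure unprotected exposure. They do not, given 24-hour reporting and ad hoc meetings.
- That primary endpoint 3, which refers to vaccine-related SAEs, would lose device-related ones. Section 14.3 reports all adverse events by seriousness and relation to Investigational Product, so that is a matter of wording.

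**Conclusion.** The point holds in a narrow form. Criteria 1 and 2 use a narrower term than the causality judgement the protocol collects, and the device's place within that judgement is inconsistent. Read literally, one non-fatal, non-allergic, non-local SAE attributed to the TDS-IM or the electroporation procedure and not to the vaccine does not trigger the automatic stop and the 2-business-day SRB review. The same applies, less plausibly, to a death.

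The size cannot be given as a number. The protocol states no rate for such events, so neither a probability nor a count of missed pauses can be derived. The conclusion rests on the wording of Section 17.3 as it stands. The Study Operations Manual, which holds further SAE and PSRT detail, is not available here and may narrow the gap further. This is a worthwhile safety clarification, not a fault that undermines the trial.

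**What to change.** In Section 17.3, criteria 1 and 2, replace the reference to the investigational vaccine(s) with: Investigational Product, including the TDS-IM device and EP administration. In Section 10.3, state that causality is assessed on that same definition, so that the rating collected is the rating that triggers the pause.

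The cost is a wording change and one sentence. No visit, procedure or volunteer is added. The downside is that pauses may be slightly more frequent, each needing an SRB review before dosing resumes.

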#### **17.4 Study Supervision**

The SRB, the IAVI Chief Medical Officer (CMO) and the IAVI Medical Monitor(s) have access to progress report(s) of this study. Close cooperation will be necessary to track study progress, respond to queries about proper study implementation and management, address issues in a timely manner, and assure consistent documentation, and share information effectively. Rates of accrual, retention, and other parameters relevant to the site's performance will be regularly and closely monitored by the study team, as well as the SRB.

#### **17.5 Study Monitoring**

On-site monitoring will be conducted to ensure that the study is conducted in compliance with human subjects' protection and other research regulations and guidelines, recorded and reported in accordance with the protocol, is consistent with SOPs, GCP, applicable regulatory requirements and locally accepted practices. The monitor will confirm the quality and accuracy of data at the site by validation of CRFs against the source documents, such as clinical records. The investigators, as well as volunteers through consenting to the study, agree that the monitor may inspect study facilities and source records (e.g., informed consent forms, clinic and laboratory records, other source documents), as well as observe the performance of study procedures. Such information will be treated as strictly confidential and will under no circumstances be made publicly available.

The monitoring will adhere to GCP guidelines. The Principal Investigator will permit inspection of the facilities and all study-related documentation by authorized representatives of IAVI, and Government and Regulatory Authorities responsible for this study.

#### **17.6 Investigator's Records**

Study records include administrative documentation—including reports and correspondence relating to the study—as well as documentation related to each volunteer screened and/or enrolled in the study—including informed consent forms, case report forms, and all other source documents. The investigator will maintain and store, in a secure manner, complete, accurate, and current study records for a minimum of 2 years after marketing application approval or the study is discontinued and applicable national and local health authorities are notified. IAVI will notify the Principal Investigator of these events.

#### **18.0 INDEMNITY**

The Sponsor and Institution are responsible to have appropriate liability insurance. For research-related injuries and/or medical problems determined to result from receiving the Investigational Product, treatment including necessary emergency treatment and proper follow-up care will be made available to the volunteer free of charge at the expense of the Sponsor.

#### **19.0 PUBLICATION**

A primary manuscript describing safety and immune responses in this trial will be prepared promptly after the data analysis is available. Authors will be representatives of each CRC, the

statistical centre, the laboratories and IAVI, subject to the generally accepted criteria of contributions to the design, work, analysis and written report of the study. Manuscripts will be reviewed by representatives of each participating group, as specified in the CTA.

## **20.0 ETHICAL CONSIDERATIONS**

The Principal Investigator will ensure that the study is conducted in compliance with the protocol, SOPs in accordance with guidelines laid down by the ICH for GCP in clinical studies, the ethical principles that have their origins in the Declaration of Helsinki and applicable local standards and regulatory requirements. In addition to IEC/IRB and regulatory approvals, all other required approvals will be obtained before recruitment of volunteers, as applicable for individual sites.

## APPENDIX A: SCHEDULE OF PROCEDURES GROUPS 1-3

| Study Month                            |        | M0             |     |     |     | M1             |     |     |     | M2             |     |     |     | M3  | M5   | M6             |      |      |      | M7   | M9             | M12                    |
|----------------------------------------|--------|----------------|-----|-----|-----|----------------|-----|-----|-----|----------------|-----|-----|-----|-----|------|----------------|------|------|------|------|----------------|------------------------|
| Week                                   |        | W0             |     | W1  | W2  | W4             |     |     |     | W8             |     | W9  | W10 | W12 | W20  | W24            |      | W25  | W26  | W28  | W36            | W48 or ET  |
| Study Day                              | Screen | 0              | D3  | D7  | D14 | D28            | D31 | D35 | D42 | D56            | D59 | D63 | D70 | D84 | D140 | D168           | D171 | D175 | D182 | D196 | D252           | D336                   |
| Visit Windows (Days)                   |        | -42            | ± 1 | ± 3 | ± 3 | ± 3            | ± 1 | ± 3 | ± 3 | ± 3            | ± 1 | ± 3 | ± 3 | ± 3 | ± 3  | ± 7            | ± 1  | ± 3  | ± 3  | ± 3  | ± 7            | ± 7                    |
| Investigational Product         |        |                |     |     |     |                |     |     |     |                |     |     |     |     |      |                |      |      |      |      |                |                        |
| HIV-MAG + GENEVAX® IL12 Placebo        |        | X              |     |     |     | X              |     |     |     | X              |     |     |     |     |      |                |      |      |      |      |                |                        |
| Ad35-GRIN/ENV / Placebo                |        |                |     |     |     |                |     |     |     |                |     |     |     |     |      | X              |      |      |      |      |                |                        |
| Consent /Assessments/Counseling |        |                |     |     |     |                |     |     |     |                |     |     |     |     |      |                |      |      |      |      |                |                        |
| Informed Consent                       | X      |                |     |     |     |                |     |     |     |                |     |     |     |     |      |                |      |      |      |      |                |                        |
| Screening Assessment                   | X      |                |     |     |     |                |     |     |     |                |     |     |     |     |      |                |      |      |      |      |                |                        |
| HIV Risk Assessment                    |        | X              |     |     |     |                |     |     |     |                |     |     |     |     |      |                |      |      |      |      |                | X                      |
| HIV Risk Reduction Counseling          | X      |                |     |     |     |                |     |     |     |                |     |     |     | X   |      |                |      |      |      | X    |                | X                      |
| Pre-/Post HIV-test Counseling          | X      |                |     |     |     |                |     |     |     |                |     |     |     | X   |      |                |      |      |      | X    |                | X                      |
| Family Planning Counseling             | X      | X              |     |     |     | X              |     |     |     | X              |     |     |     |     |      | X              |      |      |      | X    | X              |                        |
| EP Tolerability Assessment             |        | X              |     |     |     | X              |     |     |     | X              |     |     |     |     |      |                |      |      |      |      |                |                        |
| Social Impact Assessment               |        |                |     |     |     |                |     |     |     |                |     |     |     |     |      |                |      |      |      |      |                | X                      |
| Clinical Safety Assessments     |        |                |     |     |     |                |     |     |     |                |     |     |     |     |      |                |      |      |      |      |                |                        |
| Comprehensive Medical History          | X      |                |     |     |     |                |     |     |     |                |     |     |     |     |      |                |      |      |      |      |                |                        |
| Interim Medical History                |        | X              | X   | X   | X   | X              | X   | X   | X   | X              | X   | X   | X   | X   | X    | X              | X    | X    | X    | X    | X  | X          |
| Concomitant Medications                | X      | X              | X   | X   | X   | X              | X   | X   | X   | X              | X   | X   | X   | X   | X    | X              | X    | X    | X    | X    |                |                        |
| General Physical Exam                  | X      |                |     |     |     |                |     |     |     |                |     |     |     |     |      |                |      |      |      |      |                | X                      |
| Directed Physical Exam                 |        | X              | X   | X   | X   | X              | X   | X   | X   | X              | X   | X   | X   | X   | X    | X              | X    | X    | X    | X    | X              |                        |
| Weight & Height                        | X      |                |     |     |     |                |     |     |     |                |     |     |     |     |      |                |      |      |      |      |                | X                      |
| Skin Pinch Test                        | X      |                |     |     |     |                |     |     |     |                |     |     |     |     |      |                |      |      |      |      |                |                        |
| Vital Signs                            | X      | X  |     |     |     | X  |     |     |     | X  |     |     |     |     |      | X  |      |      |      |      |                | X                      |
| Cervical and Axillary Lymph Nodes      | X      | X              | X   | X   | X   | X              | X   | X   | X   | X              | X   | X   | X   | X   | X    | X              | X    | X    | X    | X    | X              | X                      |
| Local and Systemic Reactogenicity      |        | X  | X   | X   |     | X  | X   | X   |     | X  | X   | X   |     |     |      | X  | X    | X    |      |      |                |                        |

| Study Month                                                                                   |        | M0  |     |     |     | M1  |     |     |     | M2  |     |     |     | M3             | M5   | M6   |      |      |      | M7             | M9   | M12                    |
|-----------------------------------------------------------------------------------------------|--------|-----|-----|-----|-----|-----|-----|-----|-----|-----|-----|-----|-----|----------------|------|------|------|------|------|----------------|------|------------------------|
| Week                                                                                          |        | W0  |     | W1  | W2  | W4  |     |     |     | W8  |     | W9  | W10 | W12            | W20  | W24  |      | W25  | W26  | W28            | W36  | W48 or ET  |
| Study Day                                                                                     | Screen | 0   | D3  | D7  | D14 | D28 | D31 | D35 | D42 | D56 | D59 | D63 | D70 | D84            | D140 | D168 | D171 | D175 | D182 | D196           | D252 | D336                   |
| Visit Windows (Days)                                                                          |        | -42 | ± 1 | ± 3 | ± 3 | ± 3 | ± 1 | ± 3 | ± 3 | ± 3 | ± 1 | ± 3 | ± 3 | ± 3            | ± 3  | ± 7  | ± 1  | ± 3  | ± 3  | ± 3            | ± 7  | ± 7                    |
|                                                                                               |        |     |     |     |     |     |     |     |     |     |     |     |     |                |      |      |      |      |      |                |      |                        |
| Adverse Events                                                                                |        | X   | X   | X   | X   | X   | X   | X   | X   | X   | X   | X   | X   | X              | X    | X    | X    | X    | X    | X              |      |                        |
| Serious Adverse Events                                                                        | X      | X   | X   | X   | X   | X   | X   | X   | X   | X   | X   | X   | X   | X              | X    | X    | X    | X    | X    | X              | X    | X                      |
| Laboratory Specimens                                                                          |        |     |     |     |     |     |     |     |     |     |     |     |     |                |      |      |      |      |      |                |      |                        |
| HIV test                                                                                      | X      |     |     |     |     |     |     |     |     |     |     |     |     | X  |      |      |      |      |      | X  |      | X          |
| Hep BsAg, anti-HepC, active syphilis                                                          | X      |     |     |     |     |     |     |     |     |     |     |     |     |                |      |      |      |      |      |                |      |                        |
| Haematology (+ plasma storage)                                                                | X      |     |     |     |     | X   |     |     |     | X   |     |     |     | X              |      | X    |      |      | X    | X              | X    | X                      |
| Clinical Chemistry (+ serum storage)                                                          | X      |     |     |     |     | X   |     |     |     | X   |     |     |     | X              |      | X    |      |      | X    | X              | X    | X                      |
| Immunology (CD4, CD8)                                                                         |        | X   |     |     |     |     |     |     |     |     |     |     |     |                |      |      |      |      |      |                |      | X                      |
| Urinalysis                                                                                    | X      | X   |     |     |     | X   |     |     |     | X   |     |     |     |                |      | X    |      |      |      |                |      | X                      |
| Pregnancy Test (all female volunteers)                                                        | X      | X   |     |     |     | X   |     |     |     | X   |     |     |     |                |      | X    |      |      |      |                | X    | X                      |
| Immunology Lab                                                                                |        |     |     |     |     |     |     |     |     |     |     |     |     |                |      |      |      |      |      |                |      |                        |
| Sample HLA Typing                                                                             |        | X   |     |     |     |     |     |     |     |     |     |     |     |                |      |      |      |      |      |                |      |                        |
| PBMCs for Cellular immunogenicity assays (ELISPOT, ICS), B cell response + PBMC storage       |        | X   |     |     |     |     |     |     | X   | X   |     |     | X   | X              |      | X    |      | X    | X    | X              | X    | X                      |
| Antibody Immunogenicity responses (HIV, Ad35 binding, neutralizing antibodies, anti-IL-12 Ab) |        | X   |     |     |     |     |     |     | X   | X   |     |     | X   | X              |      | X    |      |      | X    | X              | X    | X                      |
| Other                                                                                         |        |     |     |     |     |     |     |     |     |     |     |     |     |                |      |      |      |      |      |                |      |                        |
| Refer for IAVI Long Term Follow-Up Protocol                                                   |        |     |     |     |     |     |     |     |     |     |     |     |     |                |      |      |      |      |      |                |      | X                      |
|                                                                                               |        |     |     |     |     |     |     |     |     |     |     |     |     |                |      |      |      |      |      |                |      |                        |
| Total blood volume                                                                            | 23     | 89  |     |     |     | 9   |     |     | 80  | 98  |     |     | 80  | 103            |      | 98   |      | 30   | 98   | 103            | 98   | 103                    |
| Cumulative blood volume                                                                       |        | 112 |     |     |     | 121 |     |     | 201 | 299 |     |     | 379 | 482            |      | 580  |      | 610  | 708  | 811            | 909  | 1012                   |

 Early Termination At baseline and at least 30 min post vaccination If HIV infected, conduct ET visit and request consent for Protocol H. If ET and Protocol H visit occur on same day, do not collect PBMCs for ET visit. Performed to capture SAEs

## APPENDIX B: SCHEDULE OF PROCEDURES GROUPS 4 AND 5

| Study Month                             |        | M0             |     |     |     | M1  | M4             |      |      |      | M5   | M7             | M10            | M12                    |
|-----------------------------------------|--------|----------------|-----|-----|-----|-----|----------------|------|------|------|------|----------------|----------------|------------------------|
| Week                                    |        | W0             |     | W1  | W2  | W4  | W16            |      | W17  | W18  | W20  | W28            | W40            | W48 or ET  |
| Study Day                               | Screen | 0              | D3  | D7  | D14 | D28 | D112           | D115 | D119 | D126 | D140 | D196           | D280           | D336                   |
| Visit Windows (Days)                    |        | -42            | ± 1 | ± 3 | ± 3 | ± 3 | ± 3            | ± 3  | ± 3  | ± 3  | ± 3  | ± 7            | ± 7            | ± 7                    |
| Investigational Product          |        |                |     |     |     |     |                |      |      |      |      |                |                |                        |
| HIV-MAG + GENEVAX® IL12 / Placebo       |        | X  |     |     |     |     | X  |      |      |      |      |                |                |                        |
| Ad35-GRIN/ENV / Placebo                 |        | X  |     |     |     |     | X  |      |      |      |      |                |                |                        |
| Consent /Assessments/Counselling |        |                |     |     |     |     |                |      |      |      |      |                |                |                        |
